#### Participants and recruitment

The study population are the youngsters entering the Rotterdam youth care organisation. These youngsters are between 12 and 23 years old and have some behavioural and/or developmental problems. All youngsters in the intervention and control region will be invited to join the study. Youngsters with depressive or suicidal thoughts will be excluded from this study to avoid that the questionnaires included in this study worsen the psychological well-being of the participants.

#### Informed consent

Due to the vulnerable nature of the study population, special attention will be paid to the obtainment of informed consent. This project is performed in accordance with the code of conduct for minors [51]. The information letter and the informed consent form that are given to the youngsters also have to be signed by the parents or guardian. If necessary, the youth care professional will discuss the informed consent with the parents or guardian, especially when language or educational barriers of the parents prevent them from understanding the written text. If, during the intake procedure, the youth care professional is in contact with only one of the parents, for instance in the case of a divorce, standard procedures of youth care practice will be followed. This means that the youth care professional will communicate with the parent who is registered at the youth care organisation, and will ask the parent if there is another parent who also has to give informed consent. This procedure is used by youth care organisations because they do not want to harm the possible vulnerable relationship between parents and as they have to respect the privacy of the parents. In case the second parent responds and disapproves of the child’s participation, the child will be excluded from the study. In case the second parent does not respond, the registered parent will be asked if there might be any reason to expect that the other parent disapproves of the child’s participation in the research. If this is the case, the child will be excluded from the study. This procedure has been approved by the Medical Ethical Committee of Wageningen University.

#### Measures

The following measures are included in the three questionnaires (see for an overview Table 1).

**Table 1 T1:** Overview over measurements across the three questionnaires

**Concept**	**Indicator**	**Questionnaire T**_ **0 ** _**T**_ **1 ** _**T**_ **2** _			**Instrument**
**Personal characteristics**	Sex, age, ethnic background, education, employment	X			
**Life prospects**	Subjective health	X	X	X	2 items from SF-36
	Problem behaviour	X	X	X	SDQ
	School or employment status	X	X	X	
	Functioning at school or work	X	X	X	
**Self-regulation skills**	Planning	X	X	X	Planning subscale SRL-SRS
	Self-monitoring	X	X	X	Self-monitoring subscale SRL-SRS
	Effort	X	X	X	Effort subscale SRL-SRS
	Reflection	X	X	X	Reflection subscale SRL-SRS
**Sense of coherence**	Sense of coherence	X	X	X	Orientation to Life Questionnaire (SOC-13)
**Sport participation**	Frequency and duration	X	X	X	RSO
	Type of sport	X	X	X	RSO
	Membership sport/fitness club	X	X	X	RSO
	Sport as part of treatment plan		X		
**Sport climate**	Motivational sport climate		X	X	MCSYS

*Note.* SDQ: Strengths and Difficulties Questionnaire; SRL-SRS: Self-Regulation of Learning Self-Report Scale; RSO: Richtlijn Sportdeelname Onderzoek; MCSYS: Motivational Climate Scale for Youth Sports.

#### Life prospects

The primary outcome is the life prospects of the youngsters which will be assessed using four indicators. Subjective health of the youngsters will be assessed using two questions: “In general, how good is your health?” and “Compared to a half year ago, how would you rate your health now?”. The Strengths and Difficulties Questionnaire will be administered to measure behaviour, emotions and relationships [52]. Objective employment status (employed or unemployed) or school status (school level) will be recorded. Finally, the youngsters are asked to report how their teacher or boss would likely evaluate their work, as an indicator of school or work performance.

#### Self-regulation skills

The self-regulation skills will be assessed using the Self-Regulation of Learning Self-Report Scale [30]. The original scale consists of six subscales of which four will be used in this study. The selection is based on the relevance of the different sub-scales for the purpose of this study. The following scales will be included: planning, self-monitoring, reflection and effort.

#### Sense of coherence

Sense of coherence will be estimated using the Orientation to Life Questionnaire (SOC-13) adapted specifically for youngsters [53].

#### Sport participation

Measurements regarding sport participation will be based on the Dutch Guideline for Sport Participation Research (Richtlijn Sportdeelname Onderzoek (RSO)) with recall-periods adapted to fit the time frame of this research [54]. The items included in the questionnaire address the frequency and duration of sport activities, the type of sport activities, the membership of sport/fitness club and the inclusion of sport in the treatment plan.

#### Sample size

A power analysis using G-power has been carried out to determine the minimal sample size. The required number of participants (with the number of measurements set at 3) to find small effects (f 0.20) is 244, for a significance level of 5% and a power of 0.80. Allowing for a drop out of 20% at time 2 and 30% at time 3, a total baseline sample of 436 participants is required. The present design is expected to result in a total sample of 600 participants.

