## Methods/Design

### Study design

Quantitative and qualitative data for this study will be collected in several phases and for different purposes (see for an overview Figure 2). All the data is gathered in Rotterdam where an intervention is implemented in a youth care organisation that aims to increase the sport participation of socially vulnerable youth. The intervention will be implemented in three regions of the Rotterdam youth care organisation, two regions are in the control group where no intervention activities take place. As randomisation of the regions is not possible, the regions for the experimental and control condition are selected in such a way that the baseline characteristics of the youngsters are as similar as possible (i.e. a non-equivalent control group design). In addition, to avoid contamination, the experimental groups and the control groups are not located in adjacent regions. After describing the intervention into more detail, the data collection methods are discussed per study aim.

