#### Data analysis

Quantitative data will be analysed with the use of SPSS software (PASW statistics). The data will be analysed using multilevel modelling techniques. Single-level multiple regression models ignore the complexity of the hierarchical data within this current study and are likely to produce underestimated variances and standard errors. Multilevel modelling is especially suitable for repeated measurements of individuals nested in groups, as it is capable of examining correlated data and unequal variances [55]. In addition, because we have an unbalanced design, multilevel modelling will produce efficient estimates of the model parameters and covariance components. Within our study, the repeated measures (level 1 unit) of the individuals (level 2 unit) are nested in a region of the youth care organisation (level 3 unit). Hence, the observations are not independent from one another, because the individuals within one region are likely to be more similar as compared to other regions (i.e. between regions). For ordinal outcomes, generalized linear mixed models will be used to accommodate the different probability distributions of the data, as compared to continuous outcomes.

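### For the experimental v control contrast, the stated 244 participants and 0.80 power assume independent youngsters, although five whole regions (3 v 2) are compared

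*Protocol article*

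**What the plan says.** All places are in the protocol article.

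- **Sample size (study aim 1).** The calculation, made in G-power, reads: "The required number of participants (with the number of measurements set at 3) to find small effects (f 0.20) is 244". It is set at a 5% significance level with power 0.80. The only inflation is for attrition: "Allowing for a drop out of 20% at time 2 and 30% at time 3, a total baseline sample of 436 participants is required". A recruitment forecast follows: "The present design is expected to result in a total sample of 600 participants". The section gives no ICC, design effect or number of regions.
- **Study design.** Assignment is by region and not randomised: "The intervention will be implemented in three regions of the Rotterdam youth care organisation, two regions are in the control group".
- **Data analysis (study aim 1).** Region is the third level of the multilevel model, because "the individuals within one region are likely to be more similar as compared to other regions". The section also warns that single-level regression would give standard errors that are too small.
- **Strengths and limitations.** The causal claim is tied to comparing outcomes between the experimental and control groups. The limitations discuss non-equivalence, self-selection into sport, dilution of the intervention and the need for a large sample. They do not mention the small number of regions.

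**The concern.** The sample size rests on an assumption that the analysis section rejects. When condition is constant within a region, the experimental v control contrast is judged against variation between regions. There are five regions, so 5 - 2 = 3 between-region degrees of freedom remain for that contrast. Recruiting more youngsters per region does not add regions.

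The 0.80 is the figure against which 436 and the expected 600 look sufficient. If it does not hold for the contrast behind the causal claim, a non-significant regional difference says much less than the article implies. The limitations section points readers to headcount as the answer, and headcount cannot remove this limit.

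**Working it through.** **Inputs from the Sample size and Study design sections:** f = 0.20, alpha = 0.05, power 0.80, 3 measurements, dropout 20% then 30%, expected baseline 600, 5 regions (3 v 2). **Assumed, because the protocol does not give it:** region-level ICC of 0.005 to 0.05, with regions of equal size.

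**Step 1. Reproduce the stated figures.** The protocol does not print the test form, so it is inferred. Take a noncentral F with df (2, N - 3) and noncentrality λ = f² × N = 0.04 × N. This is the multivariate repeated-measures form with two groups and three measurements.

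- N = 243: power 0.798.
- N = 244: λ = 9.76, power 0.800.

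The match is exact and requires independent youngsters. For dropout, 244 / (0.80 × 0.70) = 435.7, hence 436. Attrition accounts for the whole inflation. The forecast of 600 corresponds to 600 × 0.80 × 0.70 = 336 completers.

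**Step 2. Add a design effect and keep the original df.** With n = N/5 per region, DE = 1 + (n - 1) × ICC and λ = 0.04 × N / DE. Example at N = 244, ICC 0.02: n = 48.8, DE = 1 + 47.8 × 0.02 = 1.96, λ = 9.76 / 1.96 = 4.99, power 0.50.

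| Assumed ICC | DE at 244 | Power at 244 | DE at 336 | Power at 336 |
|---|---|---|---|---|
| 0 | 1.00 | 0.80 | 1.00 | 0.91 |
| 0.005 | 1.24 | 0.70 | 1.33 | 0.82 |
| 0.01 | 1.48 | 0.62 | 1.66 | 0.72 |
| 0.02 | 1.96 | 0.50 | 2.32 | 0.56 |
| 0.05 | 3.39 | 0.31 | 4.31 | 0.33 |

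Power at 244 is 0.80 only at ICC 0. At 336 it holds up to an ICC of about 0.006.

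**Step 3. Use region-level df.** With 3 between-region df and 2 time contrasts, an approximate reference is F(2, 6). For ICC 0.005 / 0.01 / 0.02 / 0.05:

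- N = 244: 0.48 / 0.41 / 0.33 / 0.20.
- N = 336: 0.58 / 0.49 / 0.37 / 0.22.

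Even at ICC 0, 336 completers give 0.71 on this reference.

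**Step 4. Allow for testing change.** A stable region difference cancels from change over time, and only region-by-time variation remains. Take a difference in change of 0.40 SD, 244 completers (48.8 per region), an assumed within-person correlation of 0.7 and an assumed ICC of 0.02. With r the correlation of region effects over time:

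Variance = [2 × 0.02 × (1 - r) + 2 × (1 - 0.7) × 0.98 / 48.8] × (1/3 + 1/2), tested on t with 3 df.

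- r = 1 (stable): variance 0.0100, noncentrality 3.99, power 0.75.
- r = 0.8: variance 0.0167, noncentrality 3.09, power 0.56.
- r = 0.5: variance 0.0267, noncentrality 2.45, power 0.39.

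A single-time-point comparison under the same ICC and df gives 0.33. The size of the loss therefore depends strongly on how region effects behave over time.

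**The case against.** The case on the other side is substantial, and most of it limits the reach of the point.

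- **Hypotheses 1 to 5 concern sport participation, not region.** Participation is measured on each youngster and varies within regions, so a within-region exposure analysis does not pay the full design effect. This stands. A reader might infer that the whole design falls short of its stated power for every hypothesis. The document does not support that. The point applies to the experimental v control contrast.
- **A cross-sectional ICC is too harsh for a test of change.** This also stands, as Step 4 shows. A reader might take a single-time-point t-test on 3 df and report a drop from 0.80 to 0.55 at ICC 0, or a detectable difference of 0.61 to 1.02 SD. Those figures use a model without baseline or repeated measures. That is not the test that 244 matches, and it is not the planned analysis, so the comparison with 0.80 is not like for like.
- **The expected 600, with partial data used by the mixed model, may suffice.** This stands only for small ICCs. On the original df, ICC 0.005 gives 0.82 at 336. ICC 0.01 gives 0.81 at 480 (20% loss) and 0.85 if all 600 contribute. At ICC 0.02, all 600 give 0.66. The forecast is not presented as a clustering allowance, and effective sample size cannot exceed 5/ICC, which is 250 at ICC 0.02.
- **The multilevel model deals with clustering.** It corrects the standard errors but does not restore power.
- **Nothing is miscalculated.** This is correct. The fault is an unstated assumption that contradicts the next section. It is also not a detail left to an analysis plan, because the article prints a definite N and power.

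**Conclusion.** The point holds for the experimental v control contrast. The figures 244 and 0.80 (436 after dropout) assume independence, while the same article says youngsters within regions are not independent and assigns only five regions. At 244, any positive region-level ICC in the quantity tested takes power below 0.80.

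The direction is secure; the size is illustrative. It rests on an assumed ICC, equal region sizes, an inferred test form, and a choice of df that the article does not fix. On the original df at 336 completers, power runs from 0.82 at ICC 0.005 to 0.33 at ICC 0.05. Region-level df lower it; stable region differences with a test of change raise it. The document does not support one definite figure for the true power. Nor does it state that a null result would be read as no effect. That risk comes from leaving the five-region limit unstated.

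**What to change.** Keep recruitment and data collection as planned, and change the text in two places.

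1. **Sample size:** say that 244 and 0.80 assume no clustering by region. Then give power for the five-region (3 v 2) contrast from the planned repeated-measures model, over a labelled range: ICC 0.005 to 0.05, more and less stable region effects over time, and region-level df. Name the contrast to which the figures apply. Do not insert the detectable difference of 0.61 to 1.02 SD, which comes from a single-time-point comparison.
2. **Strengths and limitations:** add that, with five regions, a null experimental v control contrast cannot exclude effects of the planned size.

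The cost is one reworded paragraph, one added sentence and a short power calculation or simulation. No extra participants are needed. The downside is a stated power less favourable than 0.80.

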#### Data analysis

Quantitative data will be analysed with the use of SPSS software (PASW statistics). The data will be analysed using multilevel modelling techniques. Single-level multiple regression models ignore the complexity of the hierarchical data within this current study and are likely to produce underestimated variances and standard errors. Multilevel modelling is especially suitable for repeated measurements of individuals nested in groups, as it is capable of examining correlated data and unequal variances [55]. In addition, because we have an unbalanced design, multilevel modelling will produce efficient estimates of the model parameters and covariance components. Within our study, the repeated measures (level 1 unit) of the individuals (level 2 unit) are nested in a region of the youth care organisation (level 3 unit). Hence, the observations are not independent from one another, because the individuals within one region are likely to be more similar as compared to other regions (i.e. between regions). For ordinal outcomes, generalized linear mixed models will be used to accommodate the different probability distributions of the data, as compared to continuous outcomes.

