### Strengths and limitations

There has been a large amount of research investigating the positive outcomes of sport participation. These studies often draw conclusions on the association between sport and the studied outcome based on cross-sectional data. This current study aims to contribute to these findings by investigating the outcomes over a longer period of time (1.5 year) and to report on the causal effects of sport participation by comparing the outcomes of the experimental and the control group. We will explore the life experiences of socially vulnerable youth in the sport context which will allow us to draw a more comprehensive and rich picture of sport-based activities for socially vulnerable youth. In addition, the social conditions and elements of successful partnerships are studied to guide future initiatives of youth care organisations and local sport clubs to use sport as a tool for personal development. The mixed methods design of this study provides insights on the processes occurring in the black box of sport participation that may contribute to the personal development of socially vulnerable youth.

Most studies investigating the factors that influence the performance of the partnership operationalise this performance as the perceived performance by the participants. To explore this relationship for partnerships between youth care organisations and local sport clubs (research aim 4), we use a similar approach. As this part of our study takes place in the same context as the study activities to address research question 1–3, we will also be able to add objective measurements of the partnership’s performance such as the number of youngsters guided to local sport clubs and the presence of beneficial social conditions at local sport clubs.

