This study has several limitations. First of all, the quantitative part of this study has a non-equivalent control group design. The training and support given by the Care Sport Connector (CSC) is organised on a regional level, making randomisation at the individual level of the youngsters impossible. This means that the study may be subject to selection-bias if the youngsters differ on baseline characteristics between the control and the experimental groups. Secondly, due to the voluntary nature of sport participation as part of the treatment plan it is likely that the youngsters who join a sport club differ significantly on certain characteristics from the youngsters that choose not to join. This may distort the effect measurement of sport participation on life prospects, self-regulatory skills and SOC. A third limitation concerns the fact that the intervention is executed on the level of the CSC. The effect of the intervention needs to percolate to the level of the health care professionals and the youngsters, which may reduce the effect of the intervention on the outcome measures. A large sample size is needed to measure changes in life prospects of the youngsters. Fourthly, increasing the sport participation of the youngsters in the experimental groups of the Rotterdam youth care organisation is a big challenge. These youngsters are having difficulties in one or more life domains (e.g. family, school or work) and as such are not necessarily focused on engaging in sports in their leisure time. In order to be able to find significant effects of a small size, we need a large sample. Especially the administration of the third questionnaire, when the youngsters have often left the youth care organisation, will be time-consuming for the researchers. Incentives for completion of all three questionnaires are introduced to increase response rates.

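### With three intervention and two control regions, naming region as level 3 does not by itself secure valid inference for the experimental-control contrast, which has about 3 degrees of freedom

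*Protocol article*

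**What the plan says.** Allocation is by region. The Study design section states: "The intervention will be implemented in three regions of the Rotterdam youth care organisation, two regions are in the control group". It adds: "As randomisation of the regions is not possible". Strengths and limitations confirms the level of delivery: "The training and support given by the Care Sport Connector (CSC) is organised on a regional level". The same section bases the causal claim, over a follow-up of one and a half years, on "comparing the outcomes of the experimental and the control group".

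The Data analysis section under study aim 1 sets out three levels: measurements in individuals, and individuals who "are nested in a region of the youth care organisation (level 3 unit"). It gives two reasons for this model. Single-level regressions "are likely to produce underestimated variances and standard errors", and, because the design is unbalanced, "multilevel modelling will produce efficient estimates of the model parameters and covariance components". The third level is justified by the remark that "the individuals within one region are likely to be more similar as compared to other regions".

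The section does not name the group contrast as a model term. It does not say whether region has an intercept only or also its own time effect, and it gives no method for degrees of freedom. The Sample size section gives no intraclass correlation.

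**The concern.** The intervention varies only between regions, so the experimental-control comparison is a comparison of three units with two. The outcome is measured three times, so the natural form of that comparison is a difference in change.

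The stated reason for level 3, that youngsters from one region resemble each other, describes a shared level. A shared level is subtracted out when each youngster is compared with his or her own baseline. What would mislead the group-by-time contrast is regions changing at different rates for local reasons, and a region intercept does not capture that. Even when regional change is modelled, five regions in two groups leave 5 - 2 = 3 degrees of freedom for its variance, so a large-sample test relies on a variance that is poorly known.

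At stake are the interval and p-value of the contrast that carries the causal claim. A reader of the Data analysis section would conclude that clustering has been dealt with, while chance drift between regions could still be reported as an intervention effect.

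**Working it through.** **The plan's own figures.** The required 244 reproduces from a noncentral F with 2 and N - 3 df and noncentrality f² × N = 0.04 × 244 = 9.76. Power is 0.800 at 244 and 0.798 at 243. The procedure and two groups are assumed, because the article names neither. The baseline figure is 244 / (0.8 × 0.7) = 435.7, rounded up to 436. Neither step needs a clustering term.

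**Inputs.**
- Regions: 3 v 2 (Study design).
- Expected sample 600, with 20% lost by the second measurement (Sample size). With equal regions, which is an assumption, n = 600 × 0.8 / 5 = 96 per region at six months.
- ICC of change, meaning the share of the variance in change that lies between regions: not given. Range assumed: 0 to 0.05.

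**Step 1: region intercept only.** Write the change of youngster i in region j as group effect + region drift + individual residual, with total variance 1. The region intercept is absent from this expression. The model therefore uses a standard error of √[(1/3 + 1/2)/n], while the true one is √[(1/3 + 1/2)(ICC + (1 - ICC)/n)]. The ratio of true to model standard error is

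√[1 + (n - 1) × ICC].

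The type I error of a nominal 5% test is 2 × Φ(-1.96 / ratio). With n = 96:

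| ICC of change | 1 + 95 × ICC | Ratio | Type I error |
|---|---|---|---|
| 0 | 1.000 | 1.00 | 5% |
| 0.005 | 1.475 | 1.21 | 11% |
| 0.01 | 1.950 | 1.40 | 16% |
| 0.02 | 2.900 | 1.70 | 25% |
| 0.05 | 5.750 | 2.40 | 41% |

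A simulation of 400,000 trials per row agrees to within one percentage point. With 120 per region (600 and no loss), the same formula gives 5%, 12%, 19%, 29% and 46%.

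**Step 2: region-by-time effect added, normal reference.** Simulation of the restricted-likelihood fit at n = 96 gives about 4%, 7%, 9%, 11% and 13% over the same ICCs. The limiting case is an unbiased 3-df standard error read against 1.96, which rejects 14.5% of the time. The 3-df critical value is 3.18.

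**Step 3: region-level test.** A t-test on the five region mean changes with 3 df rejects 5% of the time at every ICC in the range. The mixed model with region-by-time read against t on 3 df is conservative, at 0.1% to 3.8%, because the region variance is often estimated as zero.

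**Step 4: price in power.** For illustration, take a true difference of 0.4 SD of change (the two-group equivalent of f = 0.20, since d = 2f) and n = 96. The 3-df t-test then has power 81%, 66%, 55%, 41% and 24% at ICC 0, 0.005, 0.01, 0.02 and 0.05.

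**The case against.** A reader might infer that the planned model has standard errors that are too small. The article does not support that as a statement of fact. It names no group-by-time term, does not restrict region to an intercept, and does not commit to a normal reference distribution. Random-effects structure and degrees-of-freedom method are details that a condensed article commonly leaves to the full plan, and their absence alone would be no finding. The model also includes region, so clustering is not ignored.

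Three further points count on that side:
- The inflation is nil if regions do not differ in change. The regions belong to one organisation in one city and were chosen for similar baseline characteristics. The 41% is the end of an assumed range and cannot be read as the plan's error rate.
- The hypotheses under study aim 1 concern sport participation, which varies between youngsters within a region. The 3-df argument does not carry over directly to them.
- The sentence on efficient estimation is a general reason for multilevel modelling in an unbalanced design and is not a specific claim about region.

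All of this stands, and it makes the point conditional. It does not remove it. The article does more than stay silent: it presents the three-level model as the remedy for underestimated standard errors, motivates level 3 only by similarity within regions, and promises efficient covariance components without excepting a level with five units. The group contrast is the article's own stated basis for causal inference, and the limitations concede that self-selection may distort the effect of participation itself.

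**Conclusion.** The point holds in conditional form. The region-level contrast has about 3 degrees of freedom, and the level-3 term as described does not guarantee a valid test of it. If region is fitted as an intercept only and regions differ in change, type I error at 96 per region rises from 5% to between 11% and 41% for ICCs of change of 0.005 to 0.05. If region-by-time is fitted but tested against the normal distribution, it is about 7% to 13% over the same range, and about 4% at ICC 0.

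These figures rest on equal regions, 20% loss at six months, an assumed ICC range, and group-by-time as the form of the contrast. That form is inferred from the repeated measurements and the stated group comparison.

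A small-sample test deals with chance drift between regions only. It should not be read as protection against systematic differences between regions that were not randomised. The article already acknowledges selection bias on baseline characteristics, but not regions moving apart over time or the limit set by five units.

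**What to change.** In the Data analysis section under study aim 1, for the experimental-control contrast:

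1. State the group-by-time term that carries the comparison.
2. Include a random region-by-time effect and test the contrast with small-sample degrees of freedom (Satterthwaite or Kenward-Roger). Alternatively, use a t-test on the five region mean changes with 3 df and critical value 3.18. The second is simpler and holds 5% over the range examined.
3. Make the equivalent provision for the ordinal outcomes in the generalized linear mixed models.
4. Qualify the statement on efficient covariance components so that it does not extend to the five-unit region level.
5. Say that this applies to the group contrast and not directly to the individual-level sport participation hypotheses.

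In Strengths and limitations, add that systematic differences in change between non-randomised regions cannot be separated from the intervention effect.

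No new data are needed. The cost is wider intervals and lower power for this contrast: in the illustration above, 55% at an ICC of change of 0.01 and 41% at 0.02, against the 80% planned.
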